## Methods: participants, interventions and outcomes

### Study setting {9}

We will recruit 8000 subjects from the following 78 hospitals. The list of recruitment hospitals can be found in supplementary material 1. All subjects in each treatment arm of the study will participate voluntarily after informed consent is obtained. Follow-up will be arranged at months 1, 3, 6, 12 after discharge. The project team leader communicates with the researchers of each center on a regular basis and conducts study visits in all research centers.

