### Sample size {14}

The sample size calculation was conducted using the PASS software version 25 (NCSS, LLC. Kaysville, Utah, USA). Previous studies have shown that one-year recurrence rate of stroke patients in China was 17.7% [1]. The underlying assumption was a decline of the recurrence rate of stroke from 17.7% to 14.7%. The sample size of the experimental group and the control group was about 3168 with at least 90% power and an overall two-sided alpha level of 0.05. Taking approximate dropouts of 15% into account, the number of participants recruited was estimated to be 3727 each group. Therefore, 8000 patients will be recruited for this trial.

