### Real world research settings

#### Intervention measures

In order to better reflect the efficacy of butylphthalide soft capsules in the real world, doctors will make medication plans for secondary prevention according to their condition when they are discharged, and recommend (rather than forcing) patients to take butylphthalide. The researchers will not take other interventions for the secondary prevention of patients.

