## Statistical methods

### Statistical methods for primary and secondary outcomes {20a}

The Kaplan–Meier method is used to draw the survival analysis curve of the percentage of patients with recurrent stroke within 1 month, 3 months, 6 months and 1 year of follow-up. The LogRank method is used to compare the statistical difference in the survival curve between the two groups. The COX proportional regression model is used to calculate the risk ratio (hazards ratios) and 95% CI.

The measurement data (such as NIHSS score and modified Rankin score) is expressed by x ± s, and t-test or Wilcoxon rank sum test is used for comparison between groups. The counting data (such as clinical efficacy and adverse reactions of the two groups) is expressed by chi-square test or Fisher exact test. The subgroup analysis is carried out according to sex, age, medical history and type of stroke.Propensity score matching (PSM) is taken to ensure that the covariates are balanced and comparable. A two-sided *P* value of 0.05 or less is considered statistically significant. All the analyses are done with SPSS software 18.0 or based on R software 3.4.3.

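### The stated primary log-rank test and Cox model give hospital no role, although treatment is not randomised and its recommendation, adherence support and relapse judgement all run through the hospital

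*Protocol article*

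**What the plan says.** Under Statistical methods for primary and secondary outcomes {20a}, the protocol article names Kaplan-Meier curves, a two-group log-rank test ("The LogRank method is used to compare the statistical difference in the survival curve between the two groups") and a Cox model for the hazard ratio with its 95% CI. The significance rule is "A two-sided *P* value of 0.05 or less is considered statistically significant". One further sentence says that propensity score matching will balance the covariates. It lists no covariates and does not say which analyses use the matched set. The subgroup factors are sex, age, medical history and type of stroke. Hospital appears nowhere in that section or in Sample size {14}.

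Study setting {9} says: "We will recruit 8000 subjects from the following 78 hospitals". Other sections show what passes through the hospital:

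- **Treatment.** Trial design {8} and Sequence generation {16a} leave the choice to the patient. Under Intervention measures, doctors draw up the discharge plan and "recommend (rather than forcing) patients to take butylphthalide".
- **Analysed group.** Explanation for the choice of comparators {6b} and Unblinding and allocation put good compliers in the butylphthalide group, and non-takers together with poor compliers in the control group. Strategies to improve adherence {11c} gives the medication reminders to each centre's research assistant.
- **Outcome.** Under Outcomes {12}, whether an event is a relapse or progression of the initial stroke is settled in discussion with the patient's own doctor.

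**The concern.** In a trial randomised within hospitals, leaving hospital out of the test costs mainly efficiency. Here nothing balances the two groups within hospitals. A hospital with good follow-up support may bring more patients to the compliance threshold, and so into the butylphthalide group, and may also have fewer recurrences, or record fewer. A pooled test credits that to the drug. Plans for assessment and collection of outcomes {18a} foresees removing centres with poor data, missing follow-up or high dropout, so the authors themselves allow for hospitals that differ.

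There is a second, conditional effect. If both recurrence and uptake cluster by hospital, the unstratified standard error is too small even when the two are unrelated, and the confidence interval for the hazard ratio is too narrow.

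**Working it through.** **1. The plan's own figure.** Inputs from Sample size {14}: one-year recurrence 17.7% and 14.7%, "with at least 90% power", and "an overall two-sided alpha level of 0.05". With p̄ = 0.162, the pooled two-proportion formula gives

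n = [1.960·√(2·0.162·0.838) + 1.2816·√(0.177·0.823 + 0.147·0.853)]² / 0.03² = (1.0213 + 0.6672)² / 0.0009 ≈ 3168.

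This matches the text: "The sample size of the experimental group and the control group was about 3168". With 15% dropout, 3168/0.85 = 3727.06, against 3727 stated. The arithmetic is sound. It treats patients as independent and has no hospital term. The implied hazard ratio is ln(0.853)/ln(0.823) = 0.816.

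**2. Standard error when hospital risk and uptake are unrelated.** The mean hospital size is m = 8000/78 = 102.6. The approximate variance inflation from ignoring hospital is

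1 + (m − 1) × ICC(outcome) × ICC(treatment).

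Both ICCs are assumptions.

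| ICC outcome | ICC treatment | Variance inflation | SE understated by a factor of | Type I error |
|---|---|---|---|---|
| any | 0 | 1.00 | 1.00 | 5.0% |
| 0.005 | 0.1 | 1.05 | 1.03 | 5.6% |
| 0.01 | 0.2 | 1.20 | 1.10 | 7.4% |
| 0.02 | 0.3 | 1.61 | 1.27 | 12.2% |

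Bottom row: 1 + 101.56 × 0.02 × 0.3 = 1.609 and √1.609 = 1.27. Because treatment varies within hospitals, it is the product of the two ICCs that counts. With no clustering of uptake there is no inflation.

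**3. Simulation with no drug effect.** Taken from the documents: 78 hospitals, 8000 patients, and one-year risk 16.2% (the mean of 17.7% and 14.7%). Assumed: about 103 patients per hospital, half of patients on butylphthalide on average, complete one-year follow-up, normal hospital effects, no matching. Each scenario has 1000 runs, so the Monte Carlo error is about √(0.05·0.95/1000) = 0.7 percentage points near 5%.

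| SD log hazard | SD logit uptake | Correlation | Unstratified log-rank | Stratified by hospital |
|---|---|---|---|---|
| 0.2 | 0.5 | 0 | 5.8% | 5.3% |
| 0.2 | 1.0 | 0 | 6.0% | 5.2% |
| 0.3 | 0.5 | 0 | 6.7% | 5.2% |
| 0.3 | 1.0 | 0 | 7.6% | 4.8% |
| 0.4 | 0.5 | 0 | 5.8% | 4.1% |
| 0.4 | 1.0 | 0 | 10.1% | 4.4% |
| 0.2 | 0.5 | -0.3 | 10.8% | 6.4% |
| 0.2 | 1.0 | -0.3 | 15.6% | 4.8% |
| 0.3 | 0.5 | -0.3 | 13.1% | 5.5% |
| 0.3 | 1.0 | -0.3 | 28.1% | 5.1% |
| 0.4 | 0.5 | -0.3 | 20.0% | 5.6% |
| 0.4 | 1.0 | -0.3 | 39.7% | 5.1% |

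**4. Size of the bias.** A separate simulation with 6800 patients (8000 less 15%), using person-time rate ratios, took SDs of 0.3 and 1.0 and correlation -0.3. It gave a spurious rate ratio of 0.93 unstratified, and bias near zero when stratified. On the log scale this is ln(0.93)/ln(0.816) = 0.073/0.203, or about 36% of the effect the trial is sized to find. A positive correlation would bias against the drug instead.

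**The case against.** The strongest reply is that the article is silent rather than wrong. It does not say that the test is unstratified. Strata, the propensity covariate list and the variance estimator are commonly left to a full protocol or SAP, and Dissemination plans {31a} says a full protocol exists. Hospital could be among the unlisted matching covariates. The simulations contain no matching, so none of their error rates belongs to the plan as a whole.

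Much of this stands, and it rules out several stronger readings:

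- A reader might infer that the plan disregards its 78 hospitals. The text supports only that the stated primary analyses give them no role.
- A reader might infer that local doctors determine who takes the drug. They recommend it, under the same instruction everywhere. The patient decides, and compliance then sets the group. No difference in uptake between hospitals is documented.
- A reader might infer that the standard errors are wrong in any case. They are not if uptake does not cluster by hospital.
- A reader might take 28% or 40% as the trial's false-positive rate. Those figures need an assumed correlation of -0.3 and no matching.

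What does not stand is that the matching sentence settles the matter. Balancing patient characteristics does not remove differences in local care, adherence support or event detection unless hospital enters the score or matching is done within hospital. As written, the matching is not even linked to the log-rank and Cox analyses.

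**Conclusion.** The concern holds as a weakness in the stated method, not as a demonstrated error in the result. The named log-rank and Cox analyses leave hospital out of a non-randomised comparison in which hospital is a credible confounder. A better and equally simple method is available.

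The size cannot be fixed from the documents. Under the assumed hospital SDs and without matching, type I error is about 6-10% with no correlation between hospital risk and uptake and about 11-40% at -0.3, against about 4-6% with stratification. If uptake is alike across hospitals, the problem disappears.

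Stratification deals only with differences between hospitals. It does not remove confounding between patients of the same hospital, including any that arises from grouping by compliance.

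**What to change.** Make the hospital-stratified log-rank test and the hospital-stratified Cox model primary. Match within hospital or include hospital in the propensity score, list the matching covariates, and say that the primary analyses use the matched set. Use a variance that is robust to the matching. Pool very small hospitals by a rule set in advance.

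The cost is analysis wording only, since data are already collected and uploaded by centre. The price is some precision. Hospitals where all or none of the patients are in the butylphthalide group contribute nothing to a stratified comparison. More generally, the share of information lost is roughly ICC(treatment): none if uptake is alike across hospitals, and about 30% at the top of the range used above (0.3). With about 102.6 × 0.162 = 17 events expected per hospital, most hospitals with mixed uptake should still contribute, so the loss should be slight unless uptake differs strongly between hospitals.

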### Explanation for the choice of comparators {6b}

Doctors will make medication plans for secondary prevention according to their parents’ condition when they are discharged, and recommend (rather than forcing) them to take butylphthalide. We will manage patients through Internet means such as WeChat Mini Programs, and record their medication regularly. At the end of the whole study cycle, we will take patients who take NBP for 3 months as NBP group, and patients who refused to take butylphthalide or poor drug compliance^b^ as the control group. In addition, we will faithfully record other drugs except butylphthalide soft capsules.

*b:According to the formula: “medication compliance* = *actual number of tablets / number of tablets to be taken* × *100%”, we calculate the patient’s drug compliance. 80% to 120% will be considered as good compliance, while* < *80% or* > *120% will be considered poor compliance.*

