## Trial design {8}

This study is an open-label, noninferiority, two-armed, prospective, multicenter, real world trial conducted at Northwest University in Xi’an, China. The participants will be recruited from 78 hospitals across mainland China. Eligible participants will be assigned to the butylphthalide group or the control group according to their own wills. Every researcher at each study center is scheduled to recruit patients from December 2020 to June 2023. The flow chart of the trial is shown in Fig. 1.

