## Assignment of interventions: allocation

### Sequence generation {16a}

This study is a real-world trial, with subjects assigned to this trial based on their actual conditions and wishes.

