#### Unblinding and allocation

At the end of the study cycle, the researchers will reveal the actual medication information of the patients, taking patients with good butylphthalide compliance as the butylphthalide group, and patients without taking butylphthalide and patients with poor compliance as the control group, and compare the difference of outcomes between the two groups.

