## Data collection and management

### Plans for assessment and collection of outcomes {18a}

The patient’s baseline information will be collected by the research assistant while in hospital. During follow-up period, the doctor regularly makes video calls with the patient, conducts detailed consultations with the patient, collects the patient’s follow-up information and fills it in the CRF form. Afterwards, all research data will be sorted by the research assistants of each center and uploaded to the EDC platform. The data management experts of the research center conduct a unified review of the uploaded data to ensure the accuracy and completeness of the data. We will remove those centers with poor data quality, missing follow-up information, and high dropout rates from continuing to participate in the study.

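### The NIHSS and mRS tests have no baseline term and the propensity matching is not tied to them, so a difference in starting severity can enter the comparison

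*Protocol article*

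**What the plan says.** The section on statistical methods for primary and secondary outcomes {20a} states: "The measurement data (such as NIHSS score and modified Rankin score) is expressed by x ± s, and t-test or Wilcoxon rank sum test", these tests serving to compare the two groups. It mentions no baseline score, change from baseline or covariate-adjusted model for these outcomes.

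Later in the same paragraph, after the sentence on subgroups, comes the only statement on confounding: "Propensity score matching (PSM) is taken to ensure that the covariates are balanced and comparable". It names neither the covariates nor the outcomes that the matching serves.

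The groups are not randomised:
- Trial design {8}: "Eligible participants will be assigned to the butylphthalide group or the control group according to their own wills".
- Sequence generation {16a} describes a real-world trial "with subjects assigned to this trial based on their actual conditions and wishes".
- Explanation for the choice of comparators {6b}: doctors plan discharge medication around the patient's condition and "recommend (rather than forcing) them to take butylphthalide".
- Unblinding and allocation: the final groups are set at study end by actual medication, taking "patients without taking butylphthalide and patients with poor compliance as the control group".

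According to the abstract, NIHSS is taken in the first month after discharge and the other outcomes at 1, 3, 6 and 12 months. On what is known at the start, section {18a} says only that "baseline information will be collected by the research assistant while in hospital". Table 1, which may list the items, is not shown.

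**The concern.** When patients and doctors choose the treatment, and the choice is made around the patient's condition at discharge, the two groups may well differ in severity from the start. NIHSS a month after discharge and mRS over the following year are likely to depend on where the patient began. A two-sample test on the follow-up score cannot separate that starting difference from an effect of butylphthalide. Offering the Wilcoxon test does not help, because it too ignores the starting score.

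The planned sample sharpens the problem. With thousands per group the standard error is very small, so a difference in severity too small to matter clinically can reach P < 0.05 and be read as a functional benefit or harm. Matching could prevent this, but only if severity is in the score and these tests use the matched patients. The text states neither. The test also leaves unused the precision that a recorded starting score would give.

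**Working it through.** **The plan's own figure.** The only group size given is for recurrence (Sample size {14}): 17.7% against 14.7%, 90% power, two-sided 0.05. With the pooled-variance formula,

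n = [1.960 × √(2 × 0.162 × 0.838) + 1.2816 × √(0.177 × 0.823 + 0.147 × 0.853)]² / 0.030² = (1.0213 + 0.6672)² / 0.0009 ≈ 3168,

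which is the stated number. Dividing by 0.85 gives 3727.06, against 3727 stated. This figure is sound and is not affected by the point. It is used below only as a group size; the protocol gives no sample size for NIHSS or mRS.

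**Inputs from the document:** 3168 per group; two-sided 0.05; two-sample test with no baseline term.

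**Assumed inputs (not in the document):** no treatment effect; imbalance d in starting severity of 0.02 to 0.20 SD; baseline-outcome correlation r of 0.5 to 0.7.

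**Step 1: false-positive rate of the two-sample test on unmatched groups.** In SD units the bias is d × r and the standard error is √(2/3168) = 0.0251. With k = d × r / 0.0251, the rejection rate is Φ(−1.96 − k) + 1 − Φ(1.96 − k).

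| Imbalance d (SD) | Bias, r = 0.5 | Rejects | Bias, r = 0.7 | Rejects |
|---|---|---|---|---|
| 0.02 | 0.010 | 6.8% | 0.014 | 8.6% |
| 0.05 | 0.025 | 16.9% | 0.035 | 28.6% |
| 0.10 | 0.050 | 51.2% | 0.070 | 79.6% |
| 0.20 | 0.100 | 97.8% | 0.140 | 100% |

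Self-selected groups need not be equal. If 8000 × 0.85 = 6800 completers split 1360 to 5440 (an assumed 20:80 split), the rates are 13.1% to 21.1% at 0.05 SD and 37.8% to 63.6% at 0.10 SD.

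**Step 2: what matching or adjustment does.** Simulation with no treatment effect, r = 0.6, 3168 per group, normal scores and 300 runs per row. Matching is 1:1 directly on the starting score within 0.02 SD.

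| Imbalance d (SD) | Plain t-test | ANCOVA on starting score | t-test after matching on starting score |
|---|---|---|---|
| 0 | 5.7% | 4.0% | 1.0% |
| 0.05 | 23.3% | 6.3% | 2.0% |
| 0.10 | 69.0% | 4.3% | 1.3% |
| 0.20 | 100% | 5.3% | 0.7% |

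The matched column falls below 5% because matched pairs are tested as if independent: the bias is gone and the test has become conservative. ANCOVA stays near 5%. The Wilcoxon test was not simulated; it has no baseline term either, so the same mechanism applies.

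**Step 3: precision.** A starting score with correlation r explains r² of the within-group outcome variance: 0.5² = 25% to 0.7² = 49%.

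**The case against.** The strongest objection is that the plan already names an adjustment. A t-test or Wilcoxon test on a propensity-matched sample is adjusted by design, and Step 2 shows that when severity is matched the inflation disappears. A reader might infer from {20a} that the comparison is simply unadjusted and that severity is carried into the result. The document does not support that. The matching sentence can be read as covering all outcomes, and the covariate list may stand in a full protocol or analysis plan that is not shown. Its absence from an article is not a fault.

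A reader might also argue that even after matching a trivial leftover difference would be declared significant. That cannot be shown from the document. Take an assumed NIHSS SD of 4, a slope of 0.7 and a leftover imbalance of 0.3 points: the false difference is 0.21, the standard error is 4 × √(2/3168) = 0.1005 and z = 2.09. Changing one input removes the result: a slope of 0.5 gives z = 1.49, an SD of 6 gives 1.39 and an imbalance of 0.1 gives 0.70.

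The choice between t-test and Wilcoxon, the use of mean and SD, and the display of mRS by grade are preference or analysis-plan detail. They are not part of this point.

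What remains is narrower. The tests that the article does fix have no baseline term, and the article does not tie the matching to them. The reassuring result in Step 2 comes from matching directly on the starting score, which the text does not promise.

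**Conclusion.** The point holds in a limited form. As written, the NIHSS and mRS comparisons are protected against a difference in starting severity only if two unstated conditions are met: severity is in the propensity score, and these tests use the matched set. If they are not met, an imbalance of 0.05 to 0.10 SD gives about 17% to 80% false positives at a nominal 5%. If they are met and the matching is close, there is no inflation. A model adjusted for the starting score controls measured severity in either case and also gains precision.

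These rates rest on assumed imbalances and correlations, a normal approximation and 3168 per group. They show how sensitive the test is and do not predict this trial's imbalance. Only secondary outcomes are affected; the recurrence comparison and its sample size are not. The change is worth making because it is cheap, but it does not decide the trial's main conclusion.

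**What to change.** In {20a}, state that the NIHSS and mRS comparisons are run on the matched set and that severity measured in hospital is among the covariates in the propensity score. Replace the two-sample test with a model adjusted for the starting score: linear regression (ANCOVA) for NIHSS and ordinal logistic regression for mRS.

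The cost is a little more analysis work, provided a hospital NIHSS or mRS is among the baseline data. Table 1 is not shown, so this could not be checked; if neither is recorded, one item has to be added to the baseline CRF. Recruitment was under way when the article appeared, so an added item would cover only patients enrolled afterwards unless the score can be recovered from hospital records.

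This change does not remove the bias from placing poor compliers in the control group at study end. That depends on what happens after discharge and has to be dealt with separately.

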## Objectives {7}

The objective of this trial is to confirm the efficacy and safety of butylphthalide on secondary prevention of stroke patients through follow-up of the experimental group and the control group. It provides clinical evidence for NBP to prevent and treat stroke, and has certain significance for improving treatment and prognosis of patients.

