##### Adverse events

Adverse events include emerging clinical cardiovascular events within one year (sudden death/ myocardial infarction/ arrhythmia/ heart failure, etc.), and other adverse reactions of patients in the trial group. During the follow-up period, we will add tests for other adverse reactions such as liver and kidney function, bleeding and blood coagulation.

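### Objectives {7} sets out to confirm safety, but the one method tied to adverse reactions is a significance test of difference, and a non-significant difference cannot confirm safety

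*Protocol article*

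**What the plan says.** Objectives {7} puts safety on the same footing as efficacy: "The objective of this trial is to confirm the efficacy and safety of butylphthalide on secondary prevention of stroke patients". The Discussion paragraph of the abstract and the main Discussion use a weaker verb and speak of exploring efficacy and safety.

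The Adverse events part of Outcomes {12} names the harms of interest: "Adverse events include emerging clinical cardiovascular events within one year (sudden death/ myocardial infarction/ arrhythmia/ heart failure, etc". It gives no expected rate for any of them and does not grade them by severity.

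The analysis is fixed in {20a}. For counts it reads: "The counting data (such as clinical efficacy and adverse reactions of the two groups) is expressed by chi-square test or Fisher exact test". The threshold is "A two-sided *P* value of 0.05 or less is considered statistically significant". An effect estimate with an interval is planned in the same section, "The COX proportional regression model is used to calculate the risk ratio (hazards ratios) and 95% CI", but it stands directly after the Kaplan–Meier and log-rank sentences on recurrent stroke. Matching is also listed, without being limited to an outcome: "Propensity score matching (PSM) is taken to ensure that the covariates are balanced and comparable".

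No acceptable excess of harm or upper limit appears anywhere. Trial design {8} uses the noninferiority label but gives no margin that could serve. Sample size {14} rests on recurrence alone. Under {6b} and under Unblinding and allocation, patients with poor butylphthalide compliance are analysed with the controls.

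**The concern.** A chi-square or Fisher test asks whether two proportions differ. A significant result can show harm. A non-significant one shows only that harm was not detected, which is weak information when events are few. To confirm safety, one has to rule out an excess of a stated size, and that takes an estimate, an upper confidence limit and a limit to compare it with. The objective and the named method therefore do not fit each other.

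What is at stake is the safety conclusion on sudden death, myocardial infarction and heart failure. If only a P value is reported, the reader cannot see which excess the data have excluded. The abstract says that the trial is meant to widen the use of the capsules, so unwarranted reassurance would carry weight.

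**Working it through.** **Inputs from the protocol.** Sample size {14}: recurrence 17.7% versus 14.7%, 90% power, two-sided alpha 0.05, 3168 per group, 15% dropout, 3727 per group, 8000 recruited. Equal halves of 8000 give 4000 per group; 8000 × 0.85 / 2 = 3400.

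**Inputs assumed.** One-year control rate of a listed event, 0.5% to 5%; true risk ratio 1.5. The protocol gives neither.

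**1. Reproduce the plan's figure.** n = [1.96√(2p̄(1−p̄)) + 1.2816√(p₁(1−p₁)+p₂(1−p₂))]² / (p₁−p₂)². With p₁ = 0.177, p₂ = 0.147 and p̄ = 0.162, this is (1.0213 + 0.6672)² / 0.0009 = 3168, as stated. For dropout, 3168 / 0.85 = 3727.06, which matches 3727 apart from rounding. The sizing is sound for recurrence.

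**2. Apply the same test to a 1.5-fold excess of harm.** Power = Φ{[(p₂−p₁)√n − 1.96√(2p̄(1−p̄))] / √(p₁(1−p₁)+p₂(1−p₂))}. At 1% versus 1.5% with n = 3168: (0.2814 − 0.3080) / 0.1571 = −0.169, so power is 0.43 and the chance of P>0.05 is 57%.

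| Control rate | Non-significant, 3168 per group | 3400 per group | 4000 per group |
|---|---|---|---|
| 0.5% | 76% | 74% | 71% |
| 1% | 57% | 54% | 48% |
| 2% | 28% | 25% | 18% |
| 3% | 12% | 10% | 6% |
| 5% | 1.6% | 1.1% | 0.4% |

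Below 0.5% the chance is higher still (86% at 0.25% with 3168 per group). Power reaches 80% at a control rate of 2.4% with 3168 per group, 2.2% with 3400 and 1.9% with 4000.

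Simulation agrees. With 3168 per group at 1%, power is 43% for chi-square and 39% for Fisher; at 2% it is 73% and 70%.

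**3. Vary the assumptions.** For a true doubling with 3168 per group, the chance of P>0.05 is 63% at a control rate of 0.25%, 36% at 0.5% and 9% at 1%. If matching left 1700 pairs (an illustrative number), power for the 1.5-fold excess would fall to 26% at 1% and 46% at 2%.

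**4. What an interval would show.** If the counts are equal, the upper 95% limit on the risk ratio is exp{1.96√[2(1/a − 1/n)]}, where a is the number of events per group. With n = 3168 it is 2.00 at 0.5%, 1.63 at 1%, 1.41 at 2% and 1.32 at 3%. So identical counts at 1% would not exclude a 50% excess; at 2% they would.

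Take next the expected counts under a true 1.5-fold excess at 1%: 31.7 and 47.5 events. The 95% CI is 0.96 to 2.35. The test is non-significant, yet the interval still allows more than a doubling. The P value alone hides this.

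**The case against.** A reader might infer that the plan will declare the drug safe whenever P>0.05. The protocol does not say so. It defines only what counts as significant, and the two Discussion passages speak of exploring. The main Discussion also describes the aim for harms as detection, which a two-sided comparison of counts can serve. This objection stands: no such decision rule is in the plan, and the point has to rest on the mismatch between objective and method.

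A reader might also infer that the trial is too small to see cardiac harm in general. That is not supported either. The rates and the 50% excess are assumptions. The listed events include arrhythmia and an open-ended remainder, so the combined outcome could exceed 2%, where power is about 80% or better. The section does not limit the list to serious events.

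Third, intervals and tables by component are often left to an analysis plan or full protocol that is not shown. Naming a test does not forbid estimates, and the Cox sentence is attached to recurrence by its position, not by explicit words. Matching might also be used for safety. This has force: a missing interval alone would be a weak point. But the article commits itself both to confirming safety and to a difference test for adverse reactions. These two statements clash whatever a further document adds, and matching balances covariates without supplying a bound.

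Last, an upper confidence limit is not a clean remedy here. Patients who stop butylphthalide because of harm can be moved to the control group, which can pull the limit towards safety. This stands too, and the fix has to say so.

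**Conclusion.** The point holds as a mismatch. The objective is to confirm safety; the only method explicitly tied to adverse reactions is a test whose non-rejection cannot confirm it; and no acceptable excess is stated. How much this matters depends on event rates that the protocol does not give. At assumed control rates of 0.5% to 1%, a true 1.5-fold excess would be non-significant about 48% to 76% of the time with 3168 to 4000 per group. From about 1.9% (4000 per group) to 2.4% (3168 per group) upwards, power is 80% or more, and the practical concern for an excess of that size is small. These figures assume equal groups and no loss to matching. They do not show that harm will be missed, or that the investigators intend to equate non-significance with safety. The change is worth making because it is cheap and gives the reader what the P value cannot.

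**What to change.** In {20a}, for the combined cardiovascular events and for each named component, report the one-year risk in each group, with the risk difference and the risk or hazard ratio and their 95% CIs. State that a non-significant test is not evidence of safety.

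In Objectives {7}, replace confirm with estimate for safety (or with explore, in line with the Discussion), unless an acceptable upper limit is set before the data are analysed.

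Wherever the upper limit is interpreted, note that analysing poor compliers with the controls ({6b}; Unblinding and allocation) can bias it towards safety, and that the interval does not correct this.

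The cost is a few sentences and table columns, with no extra patients or data. The downside is a more modest safety claim for rare events.
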